### 5.2. Secondary

Evaluate the sociodemographic aspects of victims of *Bothrops* envenomations;

Describe the clinical aspects of victims of *Bothrops* envenomations with alterations in the site of the bite;

Compare different laser application protocols at sites of envenomation with inflammatory manifestations;

Evaluate the safety of the laser protocol in regards to the local effects of snakebites.

## 6. STUDY DESIGN

### 6.1. Protocol description

A 2-arm, double-blind, randomized, safety, phase II clinical trial conducted at one center in Brazil.

#### b. 6.2 Study duration

All patients presenting with FMT-HVD bitten by a *Bothrops* snake will be submitted to the standard evaluation. Selected participants will be randomized to one of three treatment regimens at the time. The treatment period will last for 3 days, with 3 days of laser application. The study will run from January 2019 to July 2021.

After the follow-up of the study, the patient will be instructed to seek the study center at any time if they have a complaint related to the snakebite.

### 6.3 Preliminary analysis

A preliminary evaluation is planned for this study after the inclusion of the first 46 patients, 23 in each arm, to validate the observed proportion of improvement in the local inflammatory condition in patients and, finally, recalculate the number of patients to be included.

## 7. PATIENT SELECTION

### 7.1. Number of patients planned

The research patients will be allocated into 2 main arms:

- **Arm 1:** Thirty patients bitten by *Bothrops* snakes who received regular FMT treatment.

[figure not shown][figure not shown]

- 
- **Arm 2:** These patients will receive the laser within 30 minutes after administration of the antivenom serum at a dose of 4 J/cm^2.

**First phase T1** - first laser application and first clinical evaluation will take place as follows:

- **Arm 1**, considered control, will receive the conventional treatment from the date of admission to the hospital and will also receive the laser, but turned off, therefore without any effect.
- **Arm 2**, will receive the laser within 30 minutes after administration of the antivenom serum at a dose of 4 J/cm^2.

**Second phase T2** - The groups will receive the same laser therapy regimen to which they were randomized within 24 hours.

**Third phase T3** - 48 hours after the first application. On the 3rd day, the patient is discharged from the hospital if they are well.

### 7.2. Inclusion criteria

Patients eligible for the study must meet the following characteristics:

- a) Less than 24 hours have passed since the bite;
- b) Must be over 18 years of age;
- c) Not having performed serum therapy for the current *Bothrops* snakebite at another institution.

### 7.3. Non-inclusion criteria

- a) Patient has an established abscess or infection at the time of admission;
- b) Patient has a dry bite;
- c) Patient is pregnant;
- d) Patient is immunocompromised;

[figure not shown][figure not shown]

- 
- e) Patient is on a course of anti-inflammatory or antibiotic drugs;
  - f) Patient has diabetes mellitus (DM).

No waiver, prospective or retrospective, of deviation in any way from the inclusion/exclusion criteria can be granted to the investigators.

#### **7.4. Criteria for discontinuing treatment**

Treatment can be stopped if there is an increase in CK or inflammatory markers: pain, heat, edema, and redness or in cases of secondary infection.

#### **7.5. Criteria for study interruption**

If the study does not show benefits, for example, the control group shows improvement and the low-power laser groups do not. The presence of marked myonecrosis will also indicate the need for the discontinuation of the study.

#### **7.6. Special warnings and precautions for use – contra-indications**

The laser must not be used for:

- Eye irradiation;
- Irradiation of the fetus or uterus in pregnant patients;
- Irradiation of bleeding areas;
- Irradiation of infected areas;
- Irradiation of an area with heat hypoesthesia;
- Irradiation of the epiphyseal lines in children;
- Irradiation in children younger than 2 years old;
- Irradiation of thyroid gland, endocrine glands and testes;
- Irradiation of vagus nerves;

- 
- Irradiation in areas with malignant tumors or cancer;
  - Irradiation of the area in patients who are receiving dermatological treatment and are using photosensitive substances or in patients who are using drugs or substances that may have a photosensitizing action.

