|                                                  |                                                                                                                                                                                                                                                                                                                                                                                                                                                                                                                                                                                                                                                                                                                                                                                                |
|--------------------------------------------------|------------------------------------------------------------------------------------------------------------------------------------------------------------------------------------------------------------------------------------------------------------------------------------------------------------------------------------------------------------------------------------------------------------------------------------------------------------------------------------------------------------------------------------------------------------------------------------------------------------------------------------------------------------------------------------------------------------------------------------------------------------------------------------------------|
| 
Expected total number of patients:
 | 
d) Patient is immunocompromised;
e) Patient is on a course of anti-inflammatories or antibiotics;
f) Patient has diabetes mellitus (DM).
 
60 patients, 30 in the treatment group and 30 in the control group, stratified as follows:
 
Arm 1) Considered the control group, this arm will receive conventional treatment from the date of admission to the hospital and will also receive the protocol with the laser turned off, therefore without any effect.
 
Arm 2) This arm will receive the laser treatment within 30 minutes after the infusion of antivenom serum at a dose of 4j/cm^2.
                                                                                                                                                      |

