### 13.2 Statistical and analytical plans

Feasibility outcomes were analyzed using descriptive statistics as proportions. Trial outcomes were reported as means and standard deviations. We report the outcomes using means and standard deviations, and we conducted inferential analysis on our data in order to report the differences between the two groups. Mean values of creatine phosphokinase activity, pain intensity, circumference measurement ratio, extent of edema, difference between the bite-site temperature and that of the contralateral limb, and disability assessments, were compared using the t-test for independent samples, at 48 hours after admission. A Kaplan-Meier survival analysis with a log-rank test was performed to detect differences in the time elapsed from admission to the day of reduction by 50% in creatine phosphokinase activity, pain intensity, circumference measurement ratio, extent of edema and difference between the bite-site temperature and that of the contralateral limb between the intervention and comparator groups, at two points - on 24 and on 48 hours after admission. The comparison of the frequency of use of analgesics, secondary infections and necrosis in a follow-up of 48 hours, between the intervention and comparator groups, was made using the Chi-square or Fisher's exact test; odds ratios with 95% confidence intervals were obtained. The Kruskal-Wallis rank sum test was used to compare the disability scores between groups, for each domain score and for the summary score. Statistical analyses were performed in the R software in the IDE Rstudio environment (version 4.1.2), and the significance level of the tests was 0.05.

[figure not shown][figure not shown]

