2.6 Date of discharge from FMT-HVD: \_\_\_\_/\_\_\_\_/\_\_\_\_  
2.7 Reason: • 1-Discharge 2-Death 3-Transference  
2.8 Zone of Occurrence: • 1-Rural 2-Urban 3-Peri-urban 9-Ignored  
2.9 Place of bite: • 1-Head 2-Arm 3-Leg 4-Torso 5-Neck 6-Hand  
7-Thigh 8-Forearm 9-Foot 10-Other (Specify): \_\_\_\_\_  

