**8.7 Concomitant complaints**

• 1-No 2-Yes (Specify): \_\_\_\_\_

**8.8 Local Demonstrations:** 1-No 2-Yes

- 8.8.1 Bleeding**
- bleeding in the skin or mucous membranes
  - evident ecchymosis
  - bleeding without impairment of general condition

- 8.8.2 Edema**
- Mild - local edema of up to 2 segments
  - Moderate - local edema of 3 to 4 segments
  - Severe - local edema of 5 segments

- Circumference of the affected region (centimeters)

Right side: \_\_\_\_cm Left side: \_\_\_\_cm Odd region

Extension of the edema: \_\_\_\_cm\*

[figure not shown]

\* mark the edema on the figure, both distal and proximal to the bite (mark the place of bite with the letter P)

- 8.8.3 Lymph nodes**
- Absent • Present Size (cm): \_\_\_\_\_
  - Consistency • elastic • stony • soften
  - Sensitivity • painful • painless
  - Mobility • attached to deep planes • not attached (mobile)

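### Section 7.6 bars the laser in conditions that 7.2 and 7.3 do not screen for, while 12.1.1 prescribes it for every Arm 2 patient, so withholding could fall on one arm only

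*Protocol*

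**What the plan says.** **Contraindications.** Section 7.6 says what the laser must not be used for. The list includes "Irradiation of bleeding areas", infected areas, areas with heat hypoesthesia, tumour areas, the thyroid and other endocrine glands, the vagus nerves, and patients using photosensitising substances.

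**Eligibility.** Section 7.2 requires a bite less than 24 hours old, age over 18, and no serum therapy elsewhere for this bite. Section 7.3 excludes infection ("Patient has an established abscess or infection at the time of admission"), dry bite, pregnancy, immunocompromise, a current course of anti-inflammatories or antibiotics, and diabetes. It allows no waivers.

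**Procedure.** Section 12.1.1 has every Arm 2 patient receive the laser at the bite on D1, D2 and D3. Arm 1 receives the same device switched off. No exception is given for a patient who meets 7.6.

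**Disease and case form.** Section 4.1 names bleeding among the local effects of the venom. Attachment B (8.8.1) records on Day 1, under local manifestations, "bleeding in the skin or mucous membranes". Attachment A (2.9) offers "Place of bite: • 1-Head 2-Arm 3-Leg 4-Torso 5-Neck 6-Hand" among its sites, and 2.10 has a code for a central bite.

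**Outcomes.** Section 13.2 compares, among others, a circumference ratio and the "difference between the bite-site temperature and that of the contralateral limb".

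**The concern.** Some items of 7.6 were carried into eligibility and others were not. A patient can satisfy 7.2 and 7.3, be randomised to Arm 2, and then present a bite site that 7.6 says must not be irradiated and 12.1.1 says must be. The person applying the laser has no rule for deciding between them.

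Two things are at stake. One is safety: following 12.1.1 to the letter means irradiating against 7.6. The other is the comparison. Every item in 7.6 concerns irradiation, and a switched-off device does not irradiate. If 7.6 is consulted only once the allocation is known, it can lead to withholding in Arm 2 and has no bearing on Arm 1. Untreated patients kept in Arm 2 dilute the effect. If they were left out of Arm 2 alone, the arms would no longer be alike.

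**Working it through.** **1. Section 7.6 against 7.2 and 7.3**

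| Item in 7.6 | Screened in 7.2/7.3? |
|---|---|
| Infected areas | Yes, 7.3(a) |
| Fetus or uterus in pregnancy | Yes, 7.3(c) |
| Children (two items) | Yes, 7.2(b) |
| Bleeding areas | No |
| Heat hypoesthesia | No |
| Eye, thyroid, other endocrine glands, testes, vagus | No criterion on bite site |
| Tumour areas | Not named; 7.3(d) covers immunocompromise only |
| Photosensitising substances | Not named; 7.3(e) covers anti-inflammatories and antibiotics |

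The paediatric items have no application in an adult trial. This suggests a general device list that was not reconciled with this protocol.

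**2. Other sections.** Sections 7.4 and 11.1.1 allow treatment to stop for infection, an adverse event, or (11.1.1) by the investigator's decision. Neither names the unscreened items. Section 8.2 states that the patient and the evaluator are blinded and does not mention whoever operates the laser. Section 8.5 has products distributed by study arm. One-sided withholding is therefore neither prescribed nor prevented.

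**3. The plan's own figure.** The synopsis gives "60 patients, 30 in the treatment group and 30 in the control group, stratified as follows". There is no effect size, SD, power or dropout rate, so 60 cannot be reproduced. What follows is illustration only.

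*Inputs.* n = 30 per arm (synopsis). Means are "compared using the t-test for independent samples, at 48 hours after admission" (13.2). Alpha is 0.05, since "the significance level of the tests was 0.05" (13.2); two-sided is assumed because the side is not stated. Power of 80% is assumed. The affected share f, 5% to 30%, is assumed.

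*Detectable effect.* d = (1.960 + 0.842) × √(2/30) = 0.723 SD.

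*(a) Laser withheld in a share f of Arm 2, all patients analysed as randomised.* The effect becomes 0.723 × (1 − f). The n needed rises by 1/(1 − f)², for example 1/0.9² = 1.23 and 1/0.7² = 2.04.

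| f | Effect (SD) | Power at 30 per arm | n per arm for 80% |
|---|---|---|---|
| 5% | 0.687 | 0.76 | 34 |
| 10% | 0.651 | 0.71 | 38 |
| 20% | 0.579 | 0.61 | 47 |
| 30% | 0.506 | 0.50 | 62 |

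*(b) The same patients dropped from Arm 2 only.* Assume they fare g = 0.5 to 1 SD worse than the rest. The bias is f × g, from 0.1 × 0.5 = 0.05 SD to 0.3 × 1 = 0.30 SD. The standard error is √(1/30 + 1/(30(1 − f))), that is 0.265 at 10% and 0.285 at 30%. The two-sided type I error then rises from 0.05 to about 0.054 at the lower end and 0.18 at the upper.

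**4. Unpaired bite sites (separate point).** The case form admits midline bites, for which there is no opposite limb. Attachment B has an entry for an odd region under circumference and a temperature field for a contralateral area, but 13.2 gives no matching definition for either measure. Bite site is fixed before randomisation, so any gap falls on both arms alike. If a share f of both arms lacked one of these outcomes, power would be 0.76 at f = 10% and 0.65 at f = 30%, under the same assumptions.

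**The case against.** Section 7.6 stands in the chapter on patient selection and can be read as a check before enrolment. It forbids irradiating bleeding areas, not enrolling patients who bleed. The bleeding item on the case form covers skin and mucous membranes generally and does not record active bleeding at the irradiated point. The laser follows the antivenom infusion, and the points treated are recorded for each application, so a ticked box does not show that irradiation was barred. Chapter 11 keeps patients who stop treatment in the study for the 3 days and requires the stop to be recorded. The affected share is invented, and how withheld applications are analysed may be settled in an analysis plan that is not shown.

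Much of this stands. A reader might infer that the arms will diverge after randomisation. The documents do not support that: nothing prescribes handling by arm, and if 7.6 is applied before randomisation, or alike to both procedures, the arms stay comparable. A reader might also infer that limb-based outcomes fail altogether for bites off the limbs. That is too broad: pain, CK and extent of edema exist at any site, a lateral bite off the limbs can have a contralateral area, and at most two measures are left undefined.

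The gap between the texts remains. Nothing says that 7.6 is an eligibility check or when it is made, and 12.1.1 has no exception. Chapter 11 deals with stopping treatment, not with a first application never given.

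**Conclusion.** The contradiction between 7.2/7.3, 7.6 and 12.1.1 is in the text and does not depend on any assumed figure. As written, an Arm 2 patient with an unscreened contraindication cannot be handled in line with all three.

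The effect on the comparison is conditional. It requires that 7.6 be applied after allocation and to active laser only, which the protocol leaves open. In that case power could fall from 80% to between 71% and 50% for an affected share of 10% to 30%; these shares, the 80% and the two-sided test are assumptions. The bias in (b) requires in addition that withheld patients be dropped, which runs against the retention rule in chapter 11.

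The undefined values at unpaired sites are a minor matter of definition. They cost some precision in two measures and do not set the arms apart.

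**What to change.** Reconcile 7.3, 7.6 and 12.1.1. Whichever contraindications the sponsor keeps should form one list, checked and documented before randomisation. At later applications the same check should apply identically to active and switched-off laser, so that an application is withheld in either arm on the same grounds. The blinded evaluator, who under 12.1.1 examines the site beforehand, could complete it. Record each withheld application with its reason, and analyse patients as randomised. Which contraindications stand is for the sponsor to settle.

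The cost is a protocol amendment, one screening item, a line on the application record, and some loss of eligible patients depending on what is kept.

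For the minor point, restrict the circumference ratio and the contralateral temperature difference by rule to bite sites with a contralateral counterpart. This needs one sentence in 13.2 and leaves eligibility unchanged. Limiting entry to limb bites is not needed and would narrow the population.

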## 8 TREATMENTS

### 8.1. Research products

The action of the laser is therapeutic and for its clinical application, the dosimetry comprises the following aspects:

- A) Energy = active principle of phototherapy represented in joules (J)
- B) Dose = amount of energy per unit transferred to the tissue, measured in J/cm^2.
- C) Wavelength (CO) = defines the actions of the red laser (most superficial layer) known in the device as L1 of 660 nm of CO and infrared that reaches deeper tissues, in the device it is seen as L2 and has a wavelength of 808 nm.
- D) Light beam power is the same for both red and infrared types, always at 100 mW.

The low-intensity laser will be the portable DMC brand (Figure 1), with the semiconductor light emitting (GaAIAs), the measures used will be those of the manufacturer's protocol and will also be based on studies of envenomation in mice(25,26, 28). Thus, this study will use as a reference the energy of 4 J, a dose of 4 J/cm^2 in red and infrared laser for a period of 40 s with the power of 100 mW at 1 cm perpendicularly away from the bite lesion. There will be a photographic record in all groups and stages.

[figure not shown][figure not shown]

According to Ortiz (2001), the biomodulation effects that occur with emissions greater than 10 J per cm^2 can cause phagocytosis of leukocytes. The measure of inhibition of phagocytosis is up to 4 J cm^2. The effect of phagocytosis is avoided if the correct laser dose is applied and the device is calibrated every 6 months.

Thermography will be performed to quantify the surface temperature at the inflamed site and to measure where local blood flow is increased or decreased. Thermographic evaluation will occur before and after each application of laser therapy in the three therapeutic moments of the intervention.

## **8.2. Method of assigning patients to the group and blinding**

A randomized clinical trial is a prospective study in humans comparing the effect and value of an intervention against a control.

Randomized clinical trials should be considered when:

- A. There is uncertainty about the effect of an exposure or treatment;
- B. Exposure can be modified in the study.

Potential limitations of randomized controlled trials include:

- A. Limited generalizability of the study population.
- B. Limited generalization of the environment under study.
- C. Randomized clinical trials answer a specific study question.

The usual measures of the magnitude of effect in randomized clinical trials are relative risk and risk difference.

The method that will be used in the measurement of the research is double masking (double-blind). This implies that neither the patient nor the professional doing the evaluation knows which treatment is being given. The double-blind method tries to eliminate evaluation bias.

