### **8.3. Clinical monitoring of participants**

During this period, clinical (1x/day) and laboratory (1x/day) examinations will be performed daily. Considering the national recommendation, this study will classify the patient according to the local aspects of the lesion for laser application:

| Local Aspects | Edema    | Pain
(numerical
scale) | Temperature
(contralateral
difference) |
|----------------------|-----------------|---------------------------------------|-------------------------------------------------------|
| Light                | 1 to 2 segments | 0-3                                   | Up to 0.5 °C                                          |
| Moderate             | 3 to 4 segments | 4-7                                   | 0.6-1 °C                                              |
| Severe               | 5 segments      | 7-10                                  | More than 1 °C                                        |

\* ADAPTED (38).

c. Participants in arms 1 and 2 will receive clinical evaluation and classification and tests related to inflammation and myonecrosis will be performed during the 3 days of hospitalization.

d. For the evaluation, a clinical form will be used with data on local and systemic signs and symptoms, daily evolution of the patient, evaluation of the wound site at all verification times, demographic data and laboratory tests, and laser application. (see Appendix A).

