#### 12.1.1 Inclusion visit: D1, D2, D3

On the first day (**D1**), the patient is seen and randomized to one of the 2 groups.

- In Arm 1, patients will be part of the control, where after completing the clinical form, the signs and symptoms and collection of laboratory tests, they will receive the application of the low-power 4J laser at the site of the snakebite, but turned off.

- In Arm 2, patients, after completing the clinical form, the signs and symptoms and collection of laboratory tests, will receive the application of a low-power 4J laser at the site of the snakebite 30 minutes after the infusion of Antivenom (AV).

On the second day (**D2**), 24 hours after the first application, patients were randomized:

[figure not shown][figure not shown]

---

- In Arm 1, the control patients, after verifying the signs, symptoms and collection of laboratory tests, will receive the application of a low-power 4J laser at the site of the snakebite, but turned off.

- In Arm 2, patients will receive after the signs, symptoms and collection of laboratory tests, will receive the application of low- power laser in 4J at the site of the bite.

On the third day (D3), 48 hours after the first application, patients were randomized:

- In Arm 1, the control patients, after verifying the signs, symptoms and collection of laboratory tests, will receive the application of a low-power 4J laser at the site of the snakebite, but turned off.

- In Arm 2, patients, after verifying the signs, symptoms and collection of laboratory tests, will receive the application of a low-power 4J laser at the site of the bite.

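### The protocol claims patient and evaluator are blind, but the sham is an unlit device against a red beam and no masking or separation of roles is described

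*Protocol*

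**What the plan says.** Section 8.2 says that "neither the patient nor the professional doing the evaluation knows which treatment is being given". The rest of that section is general remarks on randomized trials; it names no means of keeping either party blind.

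The sham is described three times, each time as an inactive device. The Synopsis says the control arm "will also receive the protocol with the laser turned off, therefore without any effect". Section 7.1 says it "will also receive the laser, but turned off, therefore without any effect". Section 12.1.1 says control patients "will receive the application of the low-power 4J laser at the site of the snakebite, but turned off".

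Section 8.1 describes the active beam as having two components, one red, "known in the device as L1 of 660 nm", and one infrared at 808 nm. Both are applied for 40 s at 100 mW, 1 cm from the lesion.

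Section 8.3 describes one clinical form for the evaluation, whose content includes "evaluation of the wound site at all verification times, demographic data and laboratory tests, and laser application". Attachment A has a laser therapy table with rows for energy, dose, time, power, anatomic points and place, by day.

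On the first session, the Synopsis and section 7.1 place the active application inside a 30-minute window following antivenom, while section 12.1.1 places it 30 minutes following the infusion. None of the three gives a time relative to antivenom for the sham.

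**The concern.** A double-blind statement is only as good as the procedure behind it. Here the one feature that separates the arms, light from the probe, is something an awake adult can see, and nothing in the text hides it. A patient who knows the arm may rate pain differently for that reason alone. The analysis cannot tell that shift from a treatment effect, and no later adjustment removes it.

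Pain is among the signs by which reduced inflammation is judged (Synopsis efficacy criteria; sections 9.1 and 9.1.3). It is also one of the means compared at 48 hours in section 13.2. The trial's title claims double-blinding, so readers will treat the pain comparison as protected.

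**Working it through.** **Step 1. What the patient can see.** Control: device off (Synopsis, 7.1, 12.1.1). Active: red plus infrared (8.1). The infrared part gives no visual cue. The protocol does not use the word visible, but it calls the other part red light, and that part belongs to every active application. The cue is therefore a lit against an unlit probe.

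**Step 2. Whether anything hides it.** Section 8.2 names no procedure. Glasses appear in 8.4.3, but only as an item to clean; they are not said to be opaque, worn in both arms or used for masking. Section 8.5 has a designated researcher distribute products by arm, but does not say that this person applies the laser or is kept apart from the evaluator. Section 9.1.3 has the investigator grade the local signs, again without separating roles.

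**Step 3. When the cue arrives.** Section 12.1.1 places signs, symptoms and blood collection before each day's application. First-day clinical grading therefore precedes any exposure. By the third-day assessment, 48 hours after the first application, the patient has been through two sessions. Thermography is also done after each application (8.1), when the session has just taken place.

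**Step 4. Which outcomes are exposed.** The 48-hour comparisons of means in 13.2, against how each is recorded:

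| Outcome | Recorded as | Exposure to knowledge of arm |
|---|---|---|
| Pain intensity | Self-rated 0 to 10 (Attachment B) | Direct |
| Disability | Scores by domain and summary (13.2) | Possible |
| Circumference ratio, edema extent | Centimetres (Attachment B) | Lower |
| Temperature difference | Degrees, both sides (Attachment B) | Lower |
| CK | Laboratory value | Lowest |

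Redness is an efficacy criterion in the Synopsis and is graded under 9.1.3, but it is not among the outcomes that 13.2 compares.

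**Step 5. The form.** Section 8.3 puts laser application on the form used for evaluation. In the attachments, the laser table is in Attachment A and the clinical signs are in Attachment B. The protocol does not say what is entered for sham. If the nominal 4 J settings are written in both arms, the table reveals nothing; if actual output is written, it reveals the arm. Section 8.5 requires the energy level to be recorded for each application and does not say which of the two is meant.

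**Step 6. Illustrative size, for pain only.** The documents give no estimate of the bias, so it is assumed at 0.2 to 0.4 SD. Inputs: n = 30 per arm (Synopsis), two-sample t-test, alpha 0.05 (13.2), taken as two-sided, no true effect. With a shift of b SD, the noncentrality is b × √(n/2) = b × √15, on 2 × 30 − 2 = 58 degrees of freedom, with critical value 2.00.

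| Assumed shift b | Noncentrality | Rejection rate |
|---|---|---|
| 0 | 0 | 5.0% |
| 0.2 SD | 0.77 | 11.9% |
| 0.3 SD | 1.16 | 20.8% |
| 0.4 SD | 1.55 | 33.2% |

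**The case against.** The strongest reply is that most analysed outcomes are measured, not judged. CK, circumference, edema extent and temperature difference leave much less room for expectation. That stands, and it confines the main exposure to pain and possibly disability. It does not protect pain itself.

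Second, clinical assessment comes before each day's application, so the evaluator need not see the beam. That helps with the evaluator and with first-day grading. It does not help with the patient's own rating at 48 hours, after two sessions.

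Third, the designated researcher in 8.5 could be an unblinded operator, and the glasses in 8.4.3 could serve as masking. Either is possible, but the protocol states neither.

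Two stronger readings are tempting. A reader might infer that the form necessarily unblinds the evaluator. The text does not support this: nominal settings could be entered in both arms, and the laser table sits apart from the clinical signs. A reader might also infer that timing separates the arms throughout, because only the active session is tied to antivenom. The gap concerns the first session alone, since the second- and third-day wording treats the arms alike. The Synopsis phrase that control receives the protocol with the laser off can also be read as implying equal timing. Nor is it clear how a patient who sees only their own session would infer the arm from its timing.

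**Conclusion.** The concern holds for patient masking and for the unstated division of roles. Section 8.2 asserts blinding of patient and evaluator; the protocol's own sham works against the first, and nothing in the text secures either. The form is a conditional weakness, depending on what is entered for sham. The timing wording needs reconciling but is not in itself evidence of unblinding.

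The rates of about 12% to 33% illustrate what an assumed shift of 0.2 to 0.4 SD would do to the pain comparison. They are not an estimate of this trial's bias and do not carry over to CK or the measured limb outcomes.

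A reader might infer that unblinding took place. The documents do not show that; they show that following the plan as written would allow it. The conclusion rests on the text available, which excludes the consent pages and the figures.

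**What to change.** 1. In 8.2, state how the beam is hidden: opaque goggles or a screen over the bite site, used identically in both arms at every session.
2. In 8.2 and 8.5, state that the designated researcher applies the device and is not the evaluator, and that the evaluator is absent during application.
3. Move the laser therapy table from the evaluator's form to the laser logbook (8.5) or the treatment file (12.2), and delete laser application from the form content in 8.3.
4. Reconcile the Synopsis and 7.1 with 12.1.1 on when the first active session falls relative to antivenom. Then state that the first session has the same timing in both arms. Which timing applies is for the investigators to settle.
5. Optionally, ask patient and evaluator at 48 hours to guess the arm. This is good practice, not the correction of an error.

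The cost is a form edit, goggles or a screen, and a few sentences of text. No extra staff should be needed if the researcher already named in 8.5 takes the operator role.
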